### Outcome measurements

#### Primary outcome

The primary outcome of our trial is the response rate of IBS-Symptom Severity Score (IBS-SSS). A responder is defined as a 50% or more reduction in IBS symptoms compared to baseline [28]. IBS-SSS is a hitherto unique symptom severity questionnaire of IBS, which evaluates the condition of abdominal pain, abdominal distension, and defecation satisfaction. This definition of a responder that reports a 50% or more reduction in IBS symptoms is less disturbed by the initial severity of IBS. IBS-SSS will be assessed at baseline, week 4, week 8, week 12, and week 20 while the response rate of IBS-SSS will be assessed at week 4, week 8, week 12, and week 20.

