##### Irritable Bowel Syndrome-Quality of Life Questionnaire (IBS-QOL)

IBS-QOL reflects the union of the physical and mental well-being covering eight dimensions, which will be assessed at baseline, week 4, week 8, week 12, and week 20.

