### Sample size calculation

The sample size calculation of this superiority trial depends on our previous pilot study and literature [9]. It can be speculated that the response rates of TXYF granule and placebo will reach 70% and 40%, respectively. We calculate by the software Gpower3.1 under the setting of 80% power and 5% type I error that 42 cases of each group are needed. With a drop-out rate of 15%, accumulated 100 cases are needed and we expect to recruit 120 IBS-D patients.

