### Statistical analysis

#### Clinical data analysis

Based on the principle of intention-to-treat (ITT), all randomly assigned participants will be included in the statistical analysis. For participants who prematurely terminate this trial, outcomes of the last visit will be used as the final outcomes. Statistical analyses will be completed by SAS (version 9.4, SAS Institute, Cary, NC). Continuous variables will be presented in the form of means and standard deviations while the categorical variables will be presented in the form of counts and percentages. The primary outcome (week 4, week 8, week 12, and week 20) and the secondary outcome AR (week 12) will be assessed by using *χ*^2^ test or Fisher’s exact test. Another secondary outcome IBS-QOL (baseline, week 4, week 8, week 12, and week 20) will be assessed by using *T* test or Mann-Whitney *U* test accompanied with the Wilcoxon test. A two-sided *P* < 0.05 indicates statistical significance. For missing data, sensitivity analysis will be conducted and the optimal approach to the imputation of missing data will be proposed.

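### IBS-QOL is compared between arms by unadjusted tests although the baseline score is collected; adjusting for it would give a more precise estimate at almost no cost

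*Protocol article*

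**What the plan says.** The IBS-QOL subsection under Secondary outcome describes an eight-dimension questionnaire "which will be assessed at baseline, week 4, week 8, week 12, and week 20". Each participant therefore has a baseline score and up to four later ones.

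The Clinical data analysis subsection fixes the method: "Another secondary outcome IBS-QOL (baseline, week 4, week 8, week 12, and week 20) will be assessed by using" a T test or a Mann-Whitney U "test accompanied with the Wilcoxon test", at a two-sided 5% level. For IBS-QOL it names no covariate, change score, ANCOVA or repeated-measures model. It does not say what the Wilcoxon test compares.

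Two other passages bear on the point. The same subsection uses the last visit as the final outcome for participants who stop early. The Intervention section mentions statistical correction for diet, but does not link this to baseline IBS-QOL. The long-term efficacy subsection gives week 20 its own role.

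**The concern.** A quality-of-life score at follow-up usually correlates with the same person's score at entry. A two-sample test on follow-up scores leaves that predictable part of the variation in the error term. A T test on change scores removes some of it, but in general not the optimal amount. Either way the interval for the treatment difference is wider than the collected data allow.

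This is a method that the protocol names, not a detail it leaves open. An analysis plan that followed the sentence as written would carry the loss forward.

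Two unclear phrases add a risk of misreading. The list of visits for the tests includes baseline, and the Wilcoxon test has no stated purpose. Depending on what is meant, the report could contain a baseline significance test that answers no useful question, or within-arm P values that are mistaken for evidence of efficacy.

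**Working it through.** **The plan's own figure.** The protocol gives no SD, effect size or power for IBS-QOL. Its only calculation concerns the IBS-SSS response rate, where it assumes that "the response rates of TXYF granule and placebo will reach 70% and 40%, respectively".

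- With a pooled variance, two-sided 5% and 80% power: n = [1.960 × √(2 × 0.55 × 0.45) + 0.842 × √(0.70 × 0.30 + 0.40 × 0.60)]² / 0.30² = (1.379 + 0.565)² / 0.09 ≈ 42 per group, as stated.
- Dropout: 42 / 0.85 = 49.4, so 50 per group and 100 in total, also as stated.

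These figures reproduce and do not depend on how IBS-QOL is analysed.

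**Inputs for IBS-QOL.** There are 60 participants per arm (120 randomised 1:1). The correlation r between baseline and follow-up is assumed, with range 0.3 to 0.7. The SD is taken as equal at both visits.

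**Variance of the treatment difference, relative to a raw follow-up comparison:**

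- raw follow-up score: 1
- change score: 2(1 − r)
- ANCOVA on baseline: 1 − r²

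The reduction from ANCOVA is r² against the raw score. Against the change score it is 1 − (1 − r²) / [2(1 − r)] = 1 − (1 + r)/2 = (1 − r)/2.

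| Assumed r | Change-score variance | ANCOVA variance | Reduction vs raw score | Reduction vs change score |
|---|---|---|---|---|
| 0.3 | 1.40 | 0.91 | 9% | 35% |
| 0.5 | 1.00 | 0.75 | 25% | 25% |
| 0.7 | 0.60 | 0.51 | 49% | 15% |

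**In terms of power.** Take the effect that a raw-score test detects with 80% power at 60 per arm: (1.960 + 0.842) × √(2/60) = 0.51 SD. By the normal approximation:

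| Assumed r | Raw score | Change score | ANCOVA | 60 per arm worth, vs raw score: 60/(1 − r²) |
|---|---|---|---|---|
| 0.3 | 80% | 65.8% | 83.6% | about 66 |
| 0.5 | 80% | 80.0% | 89.9% | 80 |
| 0.7 | 80% | 95.1% | 97.5% | about 118 |

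ANCOVA is at least as precise as either alternative at every r in the range.

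**Chance baseline imbalance.** With 60 per arm, the standard error of the baseline difference is √(2/60) = 0.18 SD. A raw follow-up comparison inherits on average the fraction r of whatever imbalance occurs. At r = 0.5, an imbalance of one standard error shifts the observed difference by 0.5 × 0.18 = 0.09 SD. It is carried over in part, not in full, and over repeated randomisations it averages to zero.

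**The Wilcoxon test.** Mann-Whitney is already the rank-sum test. If the Wilcoxon test is also a rank-sum test, it repeats the first. If it is the signed-rank test, it compares each arm with its own baseline. As an illustration of the second reading, assume r = 0.5, no treatment effect and a shared improvement of 0.3 to 0.5 SD. The probability that a given arm's paired test is significant is then Φ(0.3 × √60 − 1.96) = Φ(0.36) ≈ 64% to Φ(0.5 × √60 − 1.96) = Φ(1.91) ≈ 97%. This uses the normal approximation for a paired t test, and the improvement is assumed, not taken from the protocol.

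**The case against.** The strongest reply is that the between-arm test is valid under randomisation, the outcome is secondary, no power claim rests on it, and covariates are often left to the analysis plan. The first three statements are true and limit the weight of the point. The fourth does not remove it, because the protocol names the tests and the visits, and a better method on the same data is available.

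A reader might infer more than the text supports:

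- *That the result will be biased by baseline imbalance.* It will not. A chance difference adds noise, which is the loss of precision already counted.
- *That a between-arm significance test at baseline is planned.* The bracket may only repeat the assessment schedule, or list baseline as the reference for a paired test.
- *That within-arm tests are planned, will show improvement in both arms and will be read as efficacy.* The protocol does not call the Wilcoxon test within-arm, gives no IBS-QOL data and nowhere says that within-arm change counts as efficacy. The trial is described as a comparison with placebo.
- *That the gain is simply 25% to 49%.* This holds only against raw scores with r from 0.5 to 0.7. The text does not say whether raw or change scores are tested.
- *That the IBS-SSS total score must be analysed too.* The score is collected at the same visits, but the responder definition is a chosen and justified primary endpoint. A further score analysis is a preference, not a correction.

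**Conclusion.** The point stands as an improvement in efficiency and clarity for one secondary outcome. The stated IBS-QOL comparison is valid but less precise than the collected data permit. The size of the loss depends on two things the protocol does not give: the baseline to follow-up correlation, and whether raw or change scores are compared. Over r from 0.3 to 0.7, adjustment removes between 9% and 49% of the variance in one case and between 35% and 15% in the other. These figures assume equal SDs at the two visits and refer to the T test, not to the rank-based alternative. The remarks on the baseline visit and the Wilcoxon test are conditional: each applies only if the wording means what it may mean.

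**What to change.** 1. Replace the IBS-QOL sentence with an ANCOVA of the week-12 score on arm and baseline IBS-QOL, and report the adjusted between-arm difference with its 95% CI. Give the same estimate at week 20 as the long-term result.
2. Alternatively, use a repeated-measures mixed model with baseline score, arm, visit and arm-by-visit interaction, and take the week-12 and week-20 contrasts from it. In that case say how it fits with the last-visit rule, because such a model works from the observed visits and does not need a carried-forward value. One of the two should be the main analysis, and the other a sensitivity analysis or dropped.
3. If baseline is listed because a between-arm test is intended there, replace that test with descriptive statistics by arm.
4. State what the Wilcoxon test compares. If it is paired within arm, label it descriptive and base efficacy on the between-arm difference only. If it is the rank-sum test, delete the duplicate.

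The cost is a few sentences and standard code in SAS, which the protocol already names. No new data, visits or participants are needed. The one decision to take is the handling of early terminators under the mixed model.

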#### Mechanistic data analysis

The differential expression analysis about mRNA, miRNA, lncRNA, and circRNA for all pairwise comparisons: IBS-D patients versus healthy controls, TXYF granule (pre-treatment) versus placebo (pre-treatment), TXYF granule (post-treatment) versus placebo (post-treatment), TXYF granule (pre-treatment) versus TXYF granule (post-treatment), and placebo (post-treatment) versus placebo (post-treatment), will be performed by Cuffdiff. An adjusted *P* < 0.05 (Student’s *t* test accompanied with Benjamini-Hochberg FDR adjustment) will be used as the cut-off for significantly differentially expressed genes. Pearson correlation test will be used for target gene prediction.

## Discussion

Previous meta-analysis [29] and another two clinical trials [9, 30] have demonstrated with adequate evidence that TXYF or Tongxie formula (modified TXYF) is pretty effective and safe compared with conventional medications or placebo. Disease and syndrome differentiation are the crux of TCM treatment as we know, TXYF accords with one kind of principal pathogenesis known as liver depression and spleen deficiency of IBS-D in TCM theory so it can work. Some clinical trials with TXYF did not limit the syndrome type, which could reduce statistical power and increase type 2 errors. And in previous trials, high heterogeneity in composition and manufacture of TXYF biases the clinical outcomes and also confuses mechanistic results. The design of our trial complies with rigorous methodology and quality control. TXYF granule is produced with the standardized procedure, which guarantees homogeneous active components and makes outcomes more credible. Then, there is the issue of course of treatment. Long-term follow-up reports about this kind of functional bowel disease are rare because IBS-D has the clinical feature of recurrent episodes. IBS-D has many triggers, of which diet and emotion stress show high inducibility of this disease [31, 32]. So, we prolong the treatment period to 12 weeks in order to reduce symptom relapse and obtain better long-term efficacy. This naturally brings the problem of patient compliance, which requires us more attention.

This trial not only explores the efficacy and safety of TXYF granule but also focuses on the whole transcriptome profiling of IBS-D and the therapeutic pathways of TXYF granule. A previous study has concluded that miRNAs play a pivotal role in the IBS rat model by utilizing liquid chip and qRT-PCR and might be the targets of TXYF in the treatment of IBS [33]. Other literatures have reported that in IBS-D patients, miR-199 and miR-29 are respectively involved in visceral pain and intestinal permeability [34, 35]. Our previous studies also have proved that miR-144 and miR-200 by binding to specific target mRNA play vital roles in IBS-D rats [22, 23]. However, the study on lncRNAs and circRNAs in IBS-D is as yet scarce. Although IBS-D belongs to one kind of functional bowel disease, the mucosal functions resulting from the abnormality of relevant expressed genes and gene-coding proteins have a confirmed discrepancy between IBS-D patients and healthy individuals [36]. Especially for recognized mechanisms of IBS-D including visceral sensitivity, intestinal permeability, and intestinal motility, we anticipate starting with the target genes involved the three aspects to seek for the upstream regulatory mechanism of coding and noncoding RNAs. It is precisely because of the multiplicity of mechanism in IBS-D and pleiotropic effects about herbal treatment that genetic and transcriptional level studies can provide a penetrating and comprehensive perspective on the molecular mechanism of IBS-D and therapeutic targets of TXYF. This will be the first study to probe the whole transcriptome profiling of IBS-D and also will be the first study to explore the therapeutic targets or pathways of TCM employing whole transcriptome analysis in IBS-D.

Limitations still exist in our study. Firstly, patients who underwent the first colonoscopy and biopsies may not want to have the second colonoscopy and biopsies after the treatment, especially for those with obvious remission of symptoms. We will fully communicate with them and give careful explanation and emphasize this point before the enrollment. Secondly, because of the long period of treatment and follow-up, we will encounter the problem of high drop-out rate and establishing close contact with participants is a must. In conclusion, we hope this trial will provide high-quality evidence on the effectiveness and safety of TXYF granule. We also expect to have more insight into the mechanism of IBS-D and find out specific biomarkers and pinpoint the targets of TXYF in IBS-D.

## Trial status

This is protocol version 3 dated 15 June 2019. We made further amendment on the basis of version 1 dated 30 September 2018, and we will communicate the protocol amendments to the Clinical Trials and Biomedical Ethics Committee of the First Affiliated Hospital of Guangzhou University of Chinese Medicine. Because of the COVID-19 pandemic, recruitment will delay to June 2020, and it is anticipated that this trial will be completed in December 2021.

## Data Availability

The datasets supporting the findings of our study are available from the corresponding author upon request.

## Abbreviations

IBS: Irritable bowel syndrome
TCM: Traditional Chinese medicine
IBS-D: Diarrhea-predominant irritable bowel syndrome
BM: Bowel movements
TXYF: Tong-Xie-Yao-Fang
ncRNAs: Noncoding RNAs
IBS-SSS: IBS-Symptom Severity Score
AR: Adequate relief
IBS-QOL: IBS-Quality of Life Questionnaire IBS-QOL
GMP: Good Manufacturing Practices
eCRF: Electronic Case Report Form
RNA-seq: RNA sequencing
qRT-PCR: Quantitative real-time PCR
FPKM: Fragments per kilo-base of exon per million fragments mapped
GO: Gene Ontology
KEGG: Kyoto Encyclopedia of Genes and Genomes
AEs: Adverse events
SAEs: Severe adverse events
EDC: Electronic data collection
SOP: Standard Operating Procedures
ITT: Intention-to-treat
